## Abstract

**Introduction:**

Today, the majority of young persons living with chronic conditions in high-income countries survive into adulthood and will need life-long medical follow-up. Therefore, transition programmes have been developed to facilitate transfer to adult care, and to support self-management and independence during adulthood. The Swedish Transition Effects Project Supporting Teenagers with chrONic mEdical conditionS (STEPSTONES) project aims to evaluate the effectiveness of a person-centred transition programme for empowering adolescents with congenital heart disease in transition to adulthood. To understand how the transition programme causes change and how outcomes are created, process evaluation is imperative to assess implementation, context and mechanisms of impact. This protocol aims to describe the process evaluation of the STEPSTONES transition programme.

**Methods and design:**

Medical Research Council guidance for process evaluation of complex interventions will be the guiding framework for this mixed-method study. The combination of qualitative and quantitative data will capture different aspects of programme delivery. The sample will consist of participants in the STEPSTONES randomised controlled trial (RCT), persons implementing the programme and healthcare professionals. Quantitative data will consist of protocols and routine monitoring documents from the RCT, data collected from patient registries and sociodemographic data to assess the implementation of the intervention. This data will be analysed with quantitative content analysis, along with descriptive and inferential statistics. Qualitative data will consist of participatory observations, logbooks and interviews with persons implementing the programme, participants and healthcare professionals. Analyses will be performed using qualitative content analysis to investigate mechanism of impact, context and delivery. Quantitative and qualitative data will be integrated in the final stage by using a triangulation protocol according to mixed-method guidelines.

**Ethics and dissemination:**

The study is approved by the Regional Ethical Review Board in Gothenburg, Sweden. Results will be presented in open access, peer-reviewed journals and at international scientific conferences.

Strengths and limitations of this studyThis is the first process evaluation study of a transition programme for adolescents with congenital heart disease. Therefore, the study is expected to fill a gap in current knowledge on how transition programmes produce change.The use of multiple data sources, both quantitative and qualitative, strengthens the quality of the findings by triangulation between data sources.Quantitative data in this study rely heavily on routine monitoring documents from the randomised controlled trial, which may affect the trustworthiness of the process evaluation results.Process evaluation data will be reported separately from the results from the effectiveness evaluation.

## Introduction

Today, the majority of young persons living with chronic conditions (CC) in high-income countries survive into adulthood and need life-long follow-up.^1 2^ When going from adolescence to adulthood, these young people will face challenges beyond those normally associated with this period in life.^3 4^ Thus, transition programmes have been advocated by several guidelines and consensus statements to ensure continuity of care and support self-management and independence in adulthood.^5–7^ The current knowledge emphasises that such programmes should be individually tailored, developmentally appropriate and encompass both the physical and psychosocial needs of the adolescent.^8 9^ Furthermore, they should include strategies facilitating both transition as a developmental process, and the transfer of care from a paediatric to an adult context.^5^ Transition programmes have been evaluated to some extent during the last decade, showing improvements in outcomes such as patients’ knowledge about their condition, increased self-management, reduced delay in accessing adult care and improved disease-specific indicators.^10–13^ However, only four randomised controlled trials (RCT) evaluating transition programmes were included in the recent review by the Cochrane Database of Systematic Reviews, and due to the studies lack of sufficient follow-up and rigorous design, the review concluded that existing research on transition programmes is insufficient in proving hard evidence on effects.^13^ Moreover, none of these RCTs conducted process evaluations with the aim to assess how these interventions created change by assessing the implementation process, contextual factors and the underlying mechanisms, that led to the outcomes. More evidence is therefore pivotal in explaining the process of care within transition programmes to provide knowledge on causality and replicability of these interventions.

Transition programmes are complex interventions, comprising numerous interacting ingredients. When the effectiveness of a complex intervention is evaluated, the active ingredients producing the outcome are generally unknown. Process evaluation is therefore indispensable in understanding which these active ingredients are and therefore help explain the mechanism of impact and causal pathways.^14–16^ Core elements of process evaluation studies are to investigate how complex interventions (eg, transition programmes) create outcomes, how these outcomes and the change they promote are affected by fidelity and potential moderators on the implementation process and the impact of contextual factors and participants’ engagement. Thus, process evaluation is not solely interested in whether the intended intervention produces effect, but also in unpacking ‘the black box’ of the intervention to investigate how effects are made.^17^ In addition to investigating aforementioned aspects, process evaluation studies should also explore if the intervention is evaluated properly with regards to internal and external validity of the RCT, and if the intervention can be sustained in practice.^18^ Therefore, the Swedish Transition Effects Project Supporting Teenagers with chrONic mEdical conditionS (STEPSTONES) project was established with the purpose of developing, testing and evaluating a person-centred transition programme for adolescents with congenital heart disease (CHD). This project will provide new evidence on the effects, causality and replicability of transition programmes for adolescents with CCs.

### The transition programme

The study in focus of the process evaluation reported here is the STEPSTONES project, which is a person-centred transition programme for adolescents (age 16–18.5 years) with CHD. The programme was developed from a brief transition intervention previously tested in Belgium.^19^ To adjust this intervention to the Swedish context, qualitative and quantitative preparatory studies were performed on the target population.^20–23^ Furthermore, stakeholder involvement, literature review and behavioural change theories were applied, following the protocol for developing health promoting programmes, intervention mapping.^24^ The programme aims to be generic, and thus applicable to other CCs. However, CHD was chosen as the target population of this intervention, being the most common congenital malformation in need of life-long follow-up.^25^ The programme consists of eight key components, implemented in five steps (see figure 1). A transition coordinator (TC) operating at each intervention centre delivers the programme. The TC is a specialised, paediatric nurse who has received tailored training in delivering the intervention.

**Figure 1 F1:**
[figure not shown]
Key components of Swedish Transition Effects Project Supporting Teenagers with Chronic Medical Conditions transition programme and implementation steps. TC, transition coordinator.

#### Participants and setting: RCT study

The STEPSTONES programme is evaluated through a hybrid RCT, where a longitudinal observational study is embedded within the RCT (figure 2). The study is performed in seven university hospitals in Sweden where two centres consist of an intervention group (n=70), and a comparison group (n=70) where individual randomisation is performed to either of the groups. The remaining five centres constitute additional control groups (n=70) where no contamination of the intervention is expected. The hypothesis is that adolescents randomised to receive the transition programme over a 2-year period will have a higher patient empowerment score compared with those randomised to usual care. Inclusion criteria for participants in the RCT study are: 16 years of age with CHD, Swedish speaking and literate. Their parents will also be invited to participate. The study is ongoing and will be concluded in 2021. A study protocol describing the RCT has been published.^26^ The process evaluation of the STEPSTONES project is conducted alongside the effectiveness evaluation and health economic evaluation in order to understand and explain the outcomes of the trial. Since the process evaluation is extensive, covering several different aspects of programme delivery, the full extent of this evaluation is reported in this paper.

**Figure 2 F2:**
[figure not shown]
Overview of the Swedish Transition Effects Project Supporting Teenagers with Chronic Medical Conditions randomised controlled trial (RCT) study design. TC, transition coordinator.

#### Outcome measures of the intervention

The primary outcome of patient empowerment is measured using the Gothenburg Young Persons Empowerment Scale (GYPES). GYPES has been psychometrically tested and proven to be valid for the study population.^27^ Patient empowerment is defined as ‘an enabling process or outcome arising from communication with the healthcare professional and a mutual sharing of resources over information relating to illness, which enhances the patient’s feelings of control, self-efficacy, coping abilities and ability to achieve change over their condition’.^28^ The secondary outcomes are transition readiness, disease-related knowledge, health behaviours, patient-reported health, quality of life, healthcare usage and parental uncertainty towards transfer to adult care.^26^ The process evaluation is focused on understanding how patient empowerment is achieved within the transition programme and how delivery of the intervention, participants’ engagement and contextual factors impact in achieving this outcome.

### Process evaluation of the transition programme

In accordance with the Medical Research Council’s (MRC) guidance on the process evaluation of complex interventions, key aspects of this evaluation are centred on the logic model of the intervention, the implementation, mechanism of impact and context.^17^ These aspects have a direct impact on how effectively interventions work in producing the desired outcome. The logic model of the intervention provides a structure for designing, carrying out and analysing process data.^17 29^ This model can also work as a blueprint of the intervention, describing the underlying theoretical assumptions, input (eg, theory, training and resources), how the intervention is intended to be delivered, components of the intervention and how the intervention aims to cause change.^17^ In figure 3, the logic model of the STEPSTONES transition programme is presented along with the key concepts in process evaluation according to the MRC guidance.^17^ This figure provides an overview, starting from the logic model, on how the process evaluation of the STEPSTONES transition programme is structured.

**Figure 3 F3:**
[figure not shown]
Overview of the process evaluation of the Swedish Transition Effects Project Supporting Teenagers with Chronic Medical Conditions transition programme, adapted from the Medical Research Council’s guidance. CHD, congenital heart disease.

The concept of implementation within this model focuses on how successful delivery of the intervention is accomplished and what is actually being delivered (ie, fidelity). Fidelity is described as ‘the degree to which the clinical intervention was delivered as it was intended’ and is assessed by evaluating adherence, dose and reach of each component of the intervention.^30^ Fidelity may have a direct impact on outcomes, and thus researchers cannot determine if an intervention failed due to poor implementation or to inadequacies in the programme, unless fidelity is measured.^31^ In addition, it is important to assess the process of delivering the intervention. For instance, exploring barriers and facilitators as expressed by the TCs, and how potential moderating factors (eg, quality of delivery) affect how the programme is delivered.^17 30^

The concept of mechanism of impact refers to how the activities performed within the intervention produce intended or unintended effects,^17^ in this case the main outcome of patient empowerment. The mechanism of impact for the participants from the intervention will be explored by assessing observable actions of patient empowerment. According to the programme theory, this can include if adolescents have developed the necessary skills to become the manager of their health and care, if they are engaged in the learning process about their health and care and if they remain in follow-up after the transfer to adult care. The mechanism of impact can be studied by including data on participants’ responsiveness and interaction with the intervention, their trajectory of care and by assessing possible moderators such as quality of delivery and complexity of the intervention.^17 30^

Finally, context includes factors external to the intervention, which influences implementation, or whether the mechanisms of impact act as intended within the context in which the intervention is being delivered.^17^ Contextual factors have shown to impact how the intervention is adapted locally and, in addition, shape the outcomes of the intervention.^32^ Therefore, the overall aim is to perform a process evaluation study, assessing the implementation of the programme and the contextual impact on this process in order to understand and explain the mechanisms creating the outcome of the transition programme. The research questions in relation to the key process evaluation concepts are listed together with the proposed research methods in figure 4.

**Figure 4 F4:**
[figure not shown]
Overview of Swedish Transition Effects Project Supporting Teenagers with Chronic Medical Conditions process evaluation components and data sources. TC, transition coordinator.

## Method

A mixed-method embedded design will be used, including collection, analysis and integration of quantitative and qualitative data.^33^ During the designing and planning of the data collection, the process evaluation guidance by the MRC^14^ was chosen as the methodological framework.

### Participants and setting

For the quantitative assessment, participants (n=70) and participating parents in the intervention group will be included. In addition, the TCs at the intervention centres, as well as a sample of physicians and nurses at all participating centres will be asked to participate. For the qualitative assessment, we will use a purposive subsample since it is not considered feasible to include all participants in the intervention group (n=70) in the qualitative data collection. Specifically, we will strive for variability of the participants’ characteristics in order to capture a breadth of experiences.^34^

### Data collection

Data will consist of a range of sources in order to capture different perspectives of key process variables. Quantitative and qualitative data collection will be carried out simultaneously and synthesised in the final analysis.

#### Quantitative data collection

The following data sources will be used to collect quantitative data on process measures:Enrolment formThe enrolment form is based on the five delivery steps of the intervention (see figure 1). The data allow for the measurement of adherence and attendance in the intervention for all eligible participants. Drop out from the study, non-attendance for visits and reasons for this will also be registered, which gives information about acceptability of the transition programme.
Intervention implementation formThis form will be filled out by the TC after each individual patient encounter, whether in person, by telephone, text message or email. This form contains the components of the intervention, for example, information and education about the health condition, treatment and health behaviour, and information about the adult care follow-up. It also gives information about topics covered, supportive activities and recommendations given, providing an indication about adherence, and dose delivered of the intervention to the patients. The data source will also give information on which communication channel is primarily used for contact between the TC and patients.
Adverse event (AE) reportThe occurrence of AEs will give an indication of potential attrition from the study.
Transition plansEach patient in the intervention receives a transition plan in which the care is documented. An analysis of this plan will be undertaken to understand what the main objectives were in the transition of individual patients. This analysis will estimate which components of the intervention have been delivered, the outcomes of these and how this is documented. The data from these sources will give information about the possible mechanism of impact, adherence, dose and the potential effects of moderating factors on fidelity such as patient characteristics.
Sociodemographic dataAge, sex, education level, diagnosis and pharmacotherapy, comorbidities, geographic location, living situation, country of birth, parental marital status and employment situation will be retrieved from the Swedish registry of CHD (Swedcon) and the questionnaires used in the RCT. These data will be used to examine the characteristics of participants who engage with and continue participation in the intervention, and those who do not (eg, drop outs and non-participants), and how this affects the reach of the programme.
Time-management formIn this form, the TCs register how much time is spent on performing different tasks of the transition programme, such as the preparation of visits, patient contacts, administration and contacts with other healthcare professionals. Time spent on study-related tasks (eg, recruitment, randomisation and data entry) is excluded from this form. By collecting data on time management, differences in intervention delivery between the two centres will be visible, also giving valuable information to a future implementation scenario.

#### Qualitative data collection

The qualitative data will be used to answer questions on how implementation is achieved, possible moderating factors and how the participants experience and engage with the intervention. Qualitative data will be collected and analysed by a researcher (MS) that is not involved in the RCT study, to ensure trustworthiness of the data.^17^ The following qualitative data sources will be used:Pair interviews with TCThroughout the course of the trial, pair interviews^35^ with the TCs will be performed every 6 months. An interview guide will be used covering topics such as the experiences of implementing the intervention, barriers and facilitators and local contextual factors.
Diary notes written by the TCReflective diary notes are requested from the TCs, describing their experiences of implementing the transition programme, barriers and facilitators and contextual factors they perceive to have affected the intervention.^36^

Participatory observationsObservations of outpatient visits will be performed to investigate how the transition programme is being implemented in practice and the responsiveness and engagement of the participants. The observations will provide data on several process variables such as fidelity, adaptations, dose and participants engagement. Both a structured observation protocol and field notes will be used. The protocol includes components from the intervention implementation form and, in addition, practical applications of how the intervention is intended to be delivered, for example, use of materials and methods to deliver the behavioural change techniques and application of person-centered care. Informal interviews will be conducted with the TCs and participants in connection with the observations as a way of ensuring trustworthiness.^37^
Observations of an information day for adolescents and their parents will be held between the second and third outpatient visit in the transition programme. During the information day, adolescents and their parents will get the opportunity to meet their peers, receive information about the adult care and discuss issues regarding transfer and transition. Participatory observations of these meetings will be performed, including informal interviews with the participants about their experiences of the day.
Semistructured interviews with adolescents and parentsParticipants and their parents will be interviewed about their experiences 1 month after completion of the transition programme. The interviews will give increased understanding of the dose received by the participants, potential moderating factors on intervention delivery, acceptability of the intervention and potential improvements for a future implementation of the transition programme into current practice.
Focus group interviews with the healthcare teamFocus group interviews will be held with interdisciplinary teams from the intervention centres. The aim is to explore what contextual factors on a local and organisational level are perceived to affect implementation and what prerequisites that are needed for a future implementation of the transition programme. The sample will consist of physicians and nurses from both paediatric cardiology and adult care with experiences of young persons with CHD.^38^

Usual care assessmentThroughout the course of the trial, the assessment of the usual care in the control and comparison groups will be undertaken through participatory observations of outpatient visits and interviews with healthcare professionals. The objective is to assess current practices, barriers and facilitators for future implementation and identify possible contamination between study sites.

### Data analysis

#### Quantitative data analysis

The process variables (eg, adherence and dose) retrieved from the enrolment form, intervention implementation form and sociodemographic data will be entered into a database and analysed in the Statistical Package for the Social Sciences by using descriptive statistics with frequency distributions, proportions, variability over time and means. The effect on process variables of intervention centres’ characteristics and patients’ sociodemographic factors will be analysed by regression analysis, as will data from the time management form, to explain potential moderators on fidelity. The reach of the intervention (ie, did the intended population participate in the study) will be assessed by comparing participants versus non-participants of the RCT with sociodemographic data and clinical data (eg, disease characteristics). The MRC guidance recommends reporting results of the process evaluation separately from the effectiveness evaluation to avoid biased interpretation of effectiveness results.^17^ We are following this recommendation but will in addition perform a post-hoc regression analysis on dose–outcome relationships as well as subgroup analysis for relevant clinical and demographical variables.

The data from the transition plans will be analysed using descriptive statistics along with quantitative content analysis^39^ using the software NVivo (QSR International Pty V.12, 2018) by counting word occurrences related to the components of the intervention to summarise what the main objectives were of each individual participant’s transition. AEs will be analysed if they occur.

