However, some challenges and limitations of this process evaluation study have to be considered. Factors affecting recruitment are not directly included in the qualitative data collection. In Steckler and Linnan’s^50^ framework, this is a part of the process evaluation which is not included in the MRC guidance.^17^ Recruitment pace, selection of study participants and recruiters’ skills could arguably be considered moderating factors on reach and outcomes. Moreover, the considerable amount of questionnaires distributed to participants in the effectiveness evaluation might affect willingness to participate and therefore adherence. That said, the acceptability of the intervention is explored and measured, and so is reach in terms of participants approached and recruited. Furthermore, the TCs performing the intervention, and their performance during the intervention, will have a great impact on many of the key process measures since they are the only personnel delivering the intervention. To manage this, data will also be collected from participants and healthcare professionals in order to broaden the perspective. Process evaluators should also be aware of how they impact the quality of the collected data (eg, Hawthorne effects), especially in participatory observations.^51^ However, a small subsample of qualitative observations from a total of 210 outpatient visits should arguably give little or no impact on effectiveness outcomes of the RCT. Nevertheless, it may affect the quality of the process evaluation results. To manage this, establishing good relations between the researchers performing the process evaluation and the TCs and healthcare professionals is important to get access to the field and retrieve trustworthy data. Informal interviews in connection with observations can also strengthen trustworthiness.^49^

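### With two intervention centres, the planned regression on centre characteristics can yield only one centre/coordinator contrast, which cannot be attributed to any characteristic

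*Protocol article*

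**What the plan says.** Under Quantitative data analysis, the article plans inferential work on process variables such as adherence and dose: "The effect on process variables of intervention centres’ characteristics and patients’ sociodemographic factors will be analysed by regression analysis". The same sentence extends regression to the time-management data and gives the purpose as accounting for moderators of fidelity. Characteristics is in the plural.

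The design behind those data is set out elsewhere:

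- Participants and setting: RCT study: "two centres consist of an intervention group (n=70), and a comparison group (n=70) where individual randomisation is performed". The other hospitals deliver nothing: "The remaining five centres constitute additional control groups (n=70) where no contamination of the intervention is expected".
- The transition programme: "A transition coordinator (TC) operating at each intervention centre delivers the programme".
- Discussion, on the coordinators: "since they are the only personnel delivering the intervention".
- Method, Participants and setting: for the quantitative assessment, "participants (n=70) and participating parents in the intervention group will be included".
- Quantitative data collection, time-management form: "differences in intervention delivery between the two centres will be visible".

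No section limits the centre part of the regression to a descriptive comparison of two sites.

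**The concern.** A regression can separate the influence of centre characteristics only if centres differ in several combinations of them. Here the fidelity data come from two centres, and each centre appears to have its own single coordinator. Any fixed feature of a centre, such as size, staffing or organisation, therefore takes exactly two values and changes exactly where centre and coordinator change.

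The interpretation of the result is at stake. The article wants to learn how context and moderators shape delivery, and its Conclusions offer this as guidance for other settings. A coefficient labelled with a centre characteristic could be read as evidence that the characteristic moderates fidelity. In fact it would be the difference between two centre-and-coordinator pairs, from which no particular cause can be singled out.

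**Working it through.** **Inputs from the article.** Intervention centres: 2. Centres without the programme, hence without fidelity data: 5. Patients in the quantitative process evaluation: 70. Coordinators per intervention centre: 1, read from the singular wording in The transition programme. The article gives no power, alpha or model equation for this regression, so there is no stated figure to reproduce.

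**Step 1: algebra.** Let C be 0 for patients at the first centre and 1 at the second. A fixed centre characteristic x_k takes the values x_k1 and x_k2, so for every patient

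x_k = x_k1 + (x_k2 − x_k1)·C.

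Every characteristic that differs between the centres is thus an exact linear function of C, and of the coordinator indicator, which equals C. If D is the (adjusted) difference in the process variable between the two centres, then:

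- One characteristic alone: b_1 = D / (x_12 − x_11). This is D in other units.
- Several characteristics: the data fix only the sum Σ b_k·(x_k2 − x_k1) = D. This is one equation in k unknowns, so the separate b_k are not identified for k ≥ 2.

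**Step 2: rank of the design matrix.** This was checked numerically for 70 patients, with arbitrary values for the characteristics and assumed splits of 35/35, 45/25 and 50/20. The result was the same for all three splits.

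| Centre characteristics (k) | Columns (intercept + k) | Rank | Rank after adding centre and coordinator indicators |
|---|---|---|---|
| 1 | 2 | 2 | 2 |
| 2 | 3 | 2 | 2 |
| 3 | 4 | 2 | 2 |
| 5 | 6 | 2 | 2 |

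**Step 3: degrees of freedom between centres.** For one characteristic, residual between-centre df = number of centres − 2 = 2 − 2 = 0. The single contrast uses up all the between-centre information. Nothing is left to show how much centres differ for other reasons, so there is no error term for a statement about centres in general.

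**Step 4: what remains estimable.** Intercept + two centre characteristics + three patient covariates: 6 columns, rank 5, so the model is deficient by one. Intercept + one centre contrast + three patient covariates: 5 columns, rank 5, so it is full rank. Patient-level coefficients are estimated from variation within centres and do not depend on the aliased part.

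**The case against.** Several points on the other side are sound and limit the criticism.

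*The regression can be run.* A reader might infer that the whole fidelity regression is inestimable. It is not. One overall centre contrast can be fitted, and the patients' sociodemographic factors in the same sentence remain estimable. Only the separate effects of centre characteristics are out of reach.

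*Standard errors.* A reader might also infer that patient-level standard errors are simply too small. That depends on the target. If the two centres are taken as fixed, a patient-level confidence interval for the difference between them is legitimate. Inflated type I error arises only when the contrast is used to speak about centres beyond these two. As illustration only, with 35 patients per centre, a simulated patient-level test at nominal 5% rejects a true null in about 9% of runs at an intraclass correlation of 0.01, 24% at 0.05 and 37% at 0.10. The correlations and the even split are assumptions; the article gives neither. The point does not rest on these figures.

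*Time-management data.* It is tempting to say that the form only compares two people. The article does not support that. The form records time by task, and the Discussion says data are gathered throughout the trial so that changes such as coordinators' learning curves can be followed. Variation within coordinator, over time and across tasks, may therefore be available. The limit applies only to differences between the centres.

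*Transparency and qualitative work.* The Discussion acknowledges that coordinators strongly influence the process measures. Interviews, diaries, focus groups and triangulation are planned to explain context. This makes it less likely that a lone coefficient would be over-read. It does not change what the regression can identify: the stated response to coordinator influence is to gather data from other informants, and the regression is left as it is.

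*Condensed article.* The list of characteristics, the coding of centre, random effects and time terms may properly sit in a fuller plan, and their absence is no fault. The aliasing is different in kind, because no specification can separate fixed centre characteristics with two centres.

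**Conclusion.** The point holds in a limited form. As written, the article promises estimates of how centre characteristics affect process variables. The design supplies one centre-level contrast, complete aliasing of every fixed characteristic with centre and coordinator, and zero residual between-centre degrees of freedom. The contrast can describe these two centres but can neither be assigned to a characteristic nor generalised.

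The conclusion depends on the number of centres, which the article states, and not on the split of the 70 patients or on any intraclass correlation. One coordinator per centre is a reading of the text. With more than one, fixed centre characteristics would still be aliased with centre. Replacement of a coordinator, or a characteristic that changed during the trial, would create some variation within centre, but the article describes neither.

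Severity is moderate. This is a secondary, explanatory analysis, reported separately from effectiveness, and it leaves the randomised comparison of empowerment scores untouched. It should still be corrected before the analysis, because the wording invites a claim about moderators that the data cannot carry.

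**What to change.** Reword the relevant sentence in Quantitative data analysis as follows:

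1. Replace regression on centre characteristics with a single centre/coordinator contrast for each process variable. Report it descriptively with a 95% CI that applies to these two centres only.
2. State that centre and coordinator cannot be separated and that the contrast will not be attributed to any one characteristic.
3. Keep regression for patient-level factors, with centre as a fixed effect.
4. Report between-centre differences in the time-management data descriptively.
5. Interpret centre differences through the coordinator interviews and diaries, the focus groups and the triangulation already planned.

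The cost is a rewording. No additional data are needed, and the only loss is a claim that two centres cannot support.
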